
### Study design

Study design is summarized in Fig. 1.

**Fig. 1 Fig1:**
[figure not shown]
Study design

The first study phase of screening begins by establishing the subject’s initial eligibility and signing of the informed consent form (ICF). Patients who choose to participate in the study will then undergo an incisional biopsy of the OPMD and, only in case of dysplasia (regardless of grading), will be included in this study and test for LOH.

LOH negative subjects who meet all other inclusion criteria, will be treated as per clinical practice (e.g., OPMD surgical excision and/or follow-up). However, information on the malignancy free-survival period will be collected for these patients at 30 months from the end of the screening phase.

LOH positive subjects will then undergo a short course (4 cycles) of immunotherapy with avelumab flat dose (800 mg iv) every 2 weeks. Four administrations of the checkpoint inhibitor avelumab have been chosen with the rationale to induce a response in lesions whose immunological derangement is expected to be less severe than in advanced cancer [10]. According to the immunoediting concept, OPMD are considered in the equilibrium phase, but the discovery of high-risk LOH could represent the initial step of immunoescape; therefore, a short course of immunotherapy could be considered sufficient to reverse such a shift in immunocompetence. Moreover, a limited number of administrations could expose patients to less risk of adverse events. This period of treatment is also consistent with other preventive trials in OPMD, both with targeted agents (cetuximab for 2 months, according to Khan et al. [11]) and immunotherapy (pembrolizumab for 4 cycles, clinicaltrials.gov: NCT02882282).

After 6 months since treatment start, excisional biopsy of OPMD will be performed or, in case of not feasibility or excessive potential morbidity of a complete resection, another incisional biopsy will be performed and LOH assessment repeated. In case of complete clinical response, the site of previous OPMD will be biopsied, to define histology and to assess LOH even in presence of normal mucosa. The 6-month timeframe to assess changes in LOH has been chosen because it is relevant for the immune system to produce a shift in genetic markers and it is a period that may be consistent with clinical practice when re-assessing a lesion for surgery.

Subjects will be followed up with clinical examinations and safety assessment every month in the first year, then every 3 months for the following 18 months. Information about OPMD recurrence and malignancy-free survival will be collected.

The duration of the study from start of enrolment to data availability for final analysis of survival will be approximately 5.5 years.

The complete flowchart of study assessment and procedures is depicted in Additional File 1.

### Statistical methodology and planned analysis

#### Sample size determination

We consider that 28 and 69% of OPMD without and with history of previous oral cavity cancer, respectively, carry high-risk OPMD. We expect to enrol about 35% of the patients of the first group (*N* = 28) and 65% of the second group (*N* = 52) (overall sample size *N* = 80 patients). Therefore, the overall number of patients with OPMD to be screened is 175. As regards the first coprimary endpoint, a sample size of 80 to 85 patients will allow to reach an 80% power for testing differences of about 13% using a one-sided binomial test for one proportion at a significance level of 2.5% (Table 1).

**Table 1 Tab1:** P0: probability of change in LOH status after 6 months of treatment with immunotherapy under the null hypothesis. P1: probability of change in LOH status after 6 months of treatment with immunotherapy under the alternative hypothesis

N	P0	P1	diff
80	0.20	0.34	0.14
80	0.17	0.30	0.13
83	0.16	0.29	0.13
85	0.19	0.32	0.13

As regards the second coprimary endpoint, a sample size of 78 to 83 patients will allow to reach a 80% power for testing differences of 20 to 22% (Table 2) using a one sample log-rank test at a significance level of 2.5% (2 years of accrual and 1 year of follow-up).

**Table 2 Tab2:** S0: recurrence or malignancy-free survival probability at 3 years under the null hypothesis. S1: recurrence or malignancy-free survival probability at 3 years under the alternative hypothesis

N	S0	S1	diff
80	0.65	0.87	0.22
81	0.60	0.82	0.22
82	0.55	0.77	0.22
82	0.50	0.72	0.22
78	0.45	0.67	0.22
83	0.40	0.61	0.21
79	0.35	0.56	0.21
80	0.30	0.50	0.20

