**Methods:**

This is a phase II, open label, single arm, multicentric trial involving Italian referral centres and expected to enrol 80 patients out of a total of 175 screened. Patients who meet all inclusion criteria and test positive for LOH after an incisional biopsy of the OPMD will undergo a short course of immunotherapy with 4 administration of avelumab. After 6 months since treatment start, resection of the entire OPMD will be performed and LOH assessment will be repeated. The follow-up for malignant transformation and safety assessment will last 30 months from the end of treatment, for a total planned study duration of approximately 5.5 years.

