## Background

Oral Potentially Malignant Disorders (OPMD) represent the most common oral precancerous condition, with an estimated prevalence rate worldwide of 4.5% [1] and, according to a recent meta-analysis, an overall potential of neoplastic transformation of 7.9% [2].

Among molecular markers, the most effective in predicting the risk of progression to oral cancer is loss of heterozygosity (LOH), which may appear in tissues regardless of their histological grade of dysplasia [3, 4]. This chromosomal profile may be found in about 28% of OPMD [5]. Patients carrying OPMD with LOH at 3p14 and/or 9p21 plus LOH at another locus have an expected 3-year risk of developing oral cancer of 35%. Moreover, when a patient previously suffered from oral cancer, the 3-year risk of malignant transformation for OPMD with defined LOH reaches 69% [6]. The presence of tumour suppressor genes at these chromosomal loci explains the potential for cancer development in presence of such alterations.

The clinical management of small OPMD is excision by electrocautery or laser. However, treatment is not always effective in preventing oral cancer. Lesions recur frequently and may subsequently progress, with tumours developing in the same or adjacent anatomical regions [7]. For larger OPMD, clinical management may be limited to lifelong surveillance as an alternative to potentially morbid repeated, multi-step surgical treatments. To improve clinical care of OPMDs, the arsenal of treatments should be expanded.

OPMD may be considered as the equilibrium phase of the immunoediting concept, i.e. a dynamic process between the tumour cells and the immune system including immunosurveillance or tumour progression [8, 9]. Thus, an imbalance in the immunosuppressive microenvironment is a possible key for malignant transformation. In this regard, the activation of the PD-1/PD-L1 pathway has a central role, witnessed by the expression of PD-L1 by multiple cell types within the OPMD microenvironment (tumour-associated macrophages, fibroblasts, lymphocytes), and by the fact that PD-L1 expression in epithelial and subepithelial cells is associated with malignant transformation [10]. The use of checkpoint inhibitors in this setting is justified by this rationale.

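### The screening number of 175 uses 69% as an LOH prevalence after oral cancer, but the only other 69% in the document is a 3-year transformation risk

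*Protocol article*

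**What the plan says.** Under Sample size determination, the protocol article opens with the planning assumption: "We consider that 28 and 69% of OPMD without and with history of previous oral cavity cancer, respectively, carry high-risk OPMD". It then splits the 80 patients to be treated into 28 without a history of oral cancer (35%) and 52 with one (65%), and concludes: "Therefore, the overall number of patients with OPMD to be screened is 175". The Methods paragraph of the abstract repeats the figure, with the trial "expected to enrol 80 patients out of a total of 175 screened".

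The Background contains both percentages. The 28% is a frequency of the LOH profile: "This chromosomal profile may be found in about 28% of OPMD". The 69% appears in a sentence about patients who have already had oral cancer, and there "the 3-year risk of malignant transformation for OPMD with defined LOH reaches 69" per cent. The companion figure in the same paragraph, for patients with LOH at 3p14 and/or 9p21 plus another locus, is a 3-year oral cancer risk of 35%.

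**The concern.** The sample size section pairs the two percentages as if they were the same kind of quantity. By the Background's account they are not. The 28% is the share of lesions with the LOH profile. The 69% is the probability of a later outcome among prior-cancer patients who already have LOH. A risk conditional on being LOH-positive says nothing about how many patients are LOH-positive, so it cannot serve as the divisor that turns enrolled patients into screened patients.

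At stake is the recruitment forecast. The prior-cancer group supplies 52 of the 80 planned patients, so most of the intended enrolment depends on this divisor. Screening also involves an incisional biopsy, so the number matters to patients and centres as well as to planning.

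**Working it through.** **Inputs.** From Sample size determination: 28 and 52 patients to enrol, assumed shares of 28% and 69%, and 175 to be screened. From the Background: what each percentage measures. From Inclusion criteria: LOH positivity means 3p14 and/or 9p21 plus at least one additional site without prior oral cancer, and 3p14 and/or 9p21 alone with prior oral cancer.

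**Reproducing 175.** Screened = enrolled / prevalence, summed over the two groups:

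- without prior cancer: 28/0.28 = 100.0
- with prior cancer: 52/0.69 = 75.4
- total: 175.4, which matches 175.

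The other natural reading applies the 35:65 split to screened rather than enrolled patients. It gives 80/(0.35 × 0.28 + 0.65 × 0.69) = 146.4, which does not match. So the 69% was used as a prevalence in the prior-cancer group.

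**Dependence on the unsupported input.** The document gives no other LOH prevalence for prior-cancer patients, so no single corrected figure can be computed. Let q be that prevalence (an assumption), and keep 28% for the other group. Then screened = 100 + 52/q. If instead about 100 + 75 patients are screened as planned, the LOH-positive yield is 28 + 75q.

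| Assumed q | Screened for 80 LOH-positive | Yield from 100 + 75 screened |
|---|---|---|
| 80% | 165 | 88 |
| 69% (plan) | 175 | 80 |
| 60% | 187 | 73 |
| 50% | 204 | about 66 |
| 40% | 230 | 58 |
| 28% | 286 | 49 |

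**What does not depend on it.** Table 1 is built from N, P0 and P1, and Table 2 from N, S0 and S1. Neither calculation takes the LOH-positive share of screened patients as an input. As a check, the exact one-sided binomial test at 2.5% with N = 80, P0 = 0.20 and P1 = 0.34 has critical value 24 and power 81%, in line with Table 1.

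**If recruitment nevertheless ended short of 80.** With the same P0 and P1, power would be 69% at 66 patients (critical value 21) and 51% at 49 patients (critical value 17). The document does not plan for this. The figures show only what a shortfall would cost.

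**The case against.** The strongest defence is that the sample size section presents an uncited planning assumption, and that the sources behind the LOH definition and the risks cannot be consulted here. A true LOH prevalence near 69% after oral cancer cannot be excluded. The LOH rule is looser for that group, since no additional site is required, so a share above 28% is plausible. This stands. It means that the 28% row is a low scenario rather than a best guess, that a prevalence above 69% would lower the number, and that 175 is unsupported rather than disproved. It does not rescue the input, because the same percentage for the same subgroup has a different meaning in the only other place it appears.

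A reader might go further in four ways that the document does not support:

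- **The trial is underpowered.** The article gives 175 as an expectation, with no rule to stop screening there, and N = 80 is fixed independently of it. A low prevalence would more naturally mean more screening.
- **The 2-year accrual period is wrong.** Neither that period nor the study duration of about 5.5 years is derived from 175.
- **The survival null hypothesis fails if the history mix shifts.** Table 2 is a grid of S0 from 0.65 to 0.30, and nothing in the text derives S0 from the 35:65 split.
- **175 should also be inflated for biopsies without dysplasia.** Study design says that patients, "only in case of dysplasia (regardless of grading), will be included in this study and test for LOH". So the word screened may already mean LOH-tested, the 28% is stated for OPMD as a whole, and no dysplasia share is given. A multiplier would be a guess and might double-count.

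**Conclusion.** The point holds as a fault in one planning input. The 175 in the abstract and the sample size section rests on 69% as the LOH-positive share after oral cancer. That conflicts with the Background's use of 69% as a 3-year transformation risk among patients who already have LOH. A transposition is the likely explanation, but it is an inference. The mismatch between the sections, and the absence of any other prevalence for this group, can be read directly from the text.

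Its size depends on the unknown prevalence: from 165 screened at 80% to 286 at 28%, with 204 at 50%. These values assume that 28% is right for patients without prior oral cancer and that the 28:52 enrolment split is kept. The treated sample size, the tests, the endpoints and both power tables are unaffected. This is a recruitment forecast to be put right, not a loss of power.

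**What to change.** Replace the 69% with a sourced LOH prevalence for patients with prior oral cancer, under the LOH definition in Inclusion criteria (3p14 and/or 9p21, no additional site), and recompute 28/0.28 + 52/q. If the 69% is a genuine prevalence, cite its source in the sample size section and distinguish it from the transformation risk in the Background. If no prevalence is available, state the screening number as a range with the assumption beside each value, as in the table above. Change the abstract to match.

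The cost is a short text change and possibly a less favourable screening figure. The treated N stays at 80.

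### One null survival value is used for two groups with 35% and 69% three-year risk, so the error rate of the survival test depends on the enrolled mix

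*Protocol article*

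**What the plan says.** All references are to the protocol article.

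- **Background.** Patients with the high-risk LOH profile and no prior oral cancer "have an expected 3-year risk of developing oral cancer of 35" per cent. With prior oral cancer, "the 3-year risk of malignant transformation for OPMD with defined LOH reaches 69" per cent. The inclusion criteria admit both groups.
- **Sample size determination, mix.** "We expect to enrol about 35% of the patients of the first group" (28 patients) and "65% of the second group" (52 patients). No cap or quota for either group is given.
- **Sample size determination, survival test.** "a sample size of 78 to 83 patients will allow to reach a 80% power for testing differences of 20 to 22" per cent, "using a one sample log-rank test at a significance level of 2.5" per cent, with "2 years of accrual and 1 year of follow-up".
- **Table 2 caption.** "S0: recurrence or malignancy-free survival probability at 3 years under the null hypothesis". Each row has one S0 for the whole sample. The eight rows run from 0.65 down to 0.30, and none is named as the null to be tested.
- **Statistical analysis.** One Kaplan-Meier curve is planned for this endpoint. Expected events by prior-cancer history are not mentioned.

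**The concern.** In a single-arm trial the null rate stands in for the control group, so an error in it goes straight into the type I error. On the article's own figures the two eligible groups differ widely in risk, and a single S0 can be right for only one mix of them. If more patients without prior cancer enrol than forecast, a pooled null is too pessimistic and an inactive drug can look effective. If fewer enrol, power is lost.

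The forecast is also fragile. It depends on 69% of screened patients with prior cancer carrying the high-risk profile, whereas the Background gives 69% as a three-year transformation risk. The two uses of that figure need to be reconciled.

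**Working it through.** **1. The plan's own figures.** The screening number reproduces: 28/0.28 + 52/0.69 = 100 + 75.4 = 175. The Table 2 sample sizes do not follow from the stated inputs. With exponential survival, 2 years of accrual, 1 year of follow-up and one-sided 2.5%, a log-hazard formula gives 70 to 75 patients, and exact-variance formulas give 50 to 65. The log-hazard formula with an unstated 10% loss comes close to all eight rows. The present point does not rest on this.

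**2. Implied null hazards.** Taking survival as exponential:

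- without prior cancer: -ln(0.65)/3 = 0.144 per year
- with prior cancer: -ln(0.31)/3 = 0.390 per year
- ratio: 0.390/0.144 = 2.7

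**3. Pooled null at the planned mix.** 0.35 × 0.65 + 0.65 × 0.31 = 0.429, a hazard of -ln(0.429)/3 = 0.282 per year. This value is derived here. The nearest Table 2 rows are 0.45 and 0.40.

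**4. Type I error by simulation.** There are 80 patients, each group keeps its own historical hazard (no drug effect), and no dropout is assumed. With O observed and E expected events, the test rejects if (O - E)/√E < -1.96. It is taken as one-sided; the article does not state the sidedness of the log-rank test. Two follow-up schemes were run: the stated 2 + 1 years, and a fixed 31.5 months (30 months after a treatment course of about six weeks).

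| Without : with prior cancer | True 3-year event-free rate | Pooled null 0.429: 2 + 1 years / fixed | Group-specific nulls |
|---|---|---|---|
| 16 : 64 (20:80) | 0.378 | 0.1% / 0.1% | about 2% |
| 28 : 52 (planned) | 0.429 | 1.0% / 1.1% | about 2% |
| 36 : 44 | 0.463 | 3.7% / 4.9% | about 2% |
| 40 : 40 (50:50) | 0.480 | 6.5% / 8.9% | about 2% |
| 46 : 34 (57:43) | 0.506 | 13.8% / 18.9% | about 2% |
| 52 : 28 (65:35) | 0.531 | 25% / 34% | about 2% |

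The 57:43 row asks what happens if 28% of both screened groups are LOH positive: 100 × 0.28 = 28 and 75.4 × 0.28 = 21.1, and 28/49.1 = 57%. The 65:35 row reverses the forecast. Both are illustrations.

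Using the exact 35:65 mixture curve as the null, instead of an exponential through 0.429, gives the same pattern under 2 + 1 years: 1.6% at the planned mix, 8.8% at 50:50 and 31% at 65:35.

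**5. Choice of row.** At the planned mix with 2 + 1 years of follow-up, S0 of 0.45, 0.40, 0.35 and 0.30 gives type I error of 0.4%, 3.4%, 17% and 48%.

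**6. Power for a hazard ratio of 0.6.**

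| Mix | Follow-up | Pooled null | Group-specific nulls |
|---|---|---|---|
| Planned | 2 + 1 years | 66% | 75% |
| Planned | fixed 31.5 months | 78% | 84% |
| 20:80 | both schemes | 40 to 50% | 79 to 87% |

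At mixes richer in patients without prior cancer the pooled test rejects more often, but only because its null is then too low.

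**The case against.** **No pooled null is fixed.** Table 2 is a planning grid, and 0.43 appears nowhere in the article. This stands, and every figure at 0.43 is conditional on that choice. It does not remove the problem, because any single S0 is tied to one mix, and step 5 shows that leaving the row open adds further uncertainty.

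**Expected events are a matter for the analysis plan.** The test is named only under sample size, and a fuller document may already compute expected events by history. That is possible. But the article itself names the test and defines its null as one probability for the whole sample, and following that as written gives the dependence shown.

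**The 35% and 69% are rates for a different event.** They are cancer risks. The endpoint also counts recurrence of OPMD with LOH and treatment-caused death. This stands: 0.65 and 0.31 are illustrative and should not be written into the analysis as they are. The Discussion also reports 74% three-year oral cancer-free survival in LOH-positive patients of the erlotinib trial, which selected on the same LOH rule. No mix of 0.65 and 0.31 can exceed 0.65, so these figures do not agree.

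**The flat 2% is true by construction.** The data were simulated from the same hazards that served as the null. This stands. Group-specific nulls remove the dependence on the mix, but not an error in the historical rates.

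**A reader might infer that the trial as planned has a type I error of 25% or more.** The article does not support that. At the forecast mix with S0 near 0.43 the test is conservative, and nothing in the article predicts a 65:35 mix.

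**Conclusion.** The point holds in a conditional form. A one-sample log-rank test with one S0 for the whole sample has an error rate that moves with the share of patients with prior oral cancer, and the article forecasts that share without controlling it. With S0 at 0.43, eight more patients without prior cancer than forecast (36 instead of 28) take the error from about 1% to between 3.7 and 4.9%, above the nominal 2.5%. A 50:50 mix takes it to between 6 and 9%. A shift the other way costs power.

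These sizes assume exponential survival, 80 patients, no dropout, a one-sided test and the cancer-only risks of the Background. The direction of the effect needs only that the two groups differ in risk.

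**What to change.** - In Statistical analysis, define expected events as the sum over patients of the null cumulative hazard for the patient's own prior-oral-cancer group, evaluated at that patient's follow-up time. This replaces the single S0.
- Fix both null rates before the analysis and justify each for the full composite: recurrence of OPMD with LOH, malignant transformation and treatment-caused death. The article gives no composite rates, so 0.144 and 0.390 per year should not be adopted without that work.
- Reconcile the Background risks with the 74% cancer-free survival cited in the Discussion, and the two meanings given to 69%.
- Show the Kaplan-Meier curve by prior-cancer group as well as overall.

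**Cost.** Analysis wording only: prior oral cancer is already needed for eligibility, so no patients, visits or data are added. The downside is that two null rates must be justified instead of one, and the result is only as sound as those rates.

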### Statistical analysis

The first coprimary endpoint is the recurrence or malignancy-free survival, for which the time is the interval from the date of the start of immunotherapy to the date of recurrence of OPMD with LOH or of malignant transformation or the date of death without recurrence/malignancy (if caused by treatment), whichever will occur first. Time will be censored at the date of last follow-up for patients alive and without events or dead for causes not related to the treatment. The recurrence or malignancy-free survival curve will be estimated with the Kaplan-Meier method.

The second co-primary endpoint is the change in LOH status (positive to negative) after 6 months of treatment with immunotherapy. The probability of change in LOH status after 6 months of treatment will be estimated with the corresponding relative frequency of patients with change among the total number of LOH positive patients at treatment start; the corresponding exact Clopper-Pearson 95% confidence interval will be estimated.

### Ethical considerations

#### Good clinical practice

This study is to be conducted according to globally accepted standards of good clinical practice (as defined in the ICH E6 Guideline for Good Clinical Practice, 1 May 1996), in agreement with the Declaration of Helsinki, in keeping with local regulations, and in compliance with the protocol. Personnel involved in conducting this study will be qualified by education, training, and experience to perform their respective tasks.

